### **7.2.3 Demographic Data and Baseline Data Analysis**

Mean, standard deviation, minimum and maximum values will be calculated for continues data in order to verify whether there is statistical difference between test group and control group regarding demographic and health statuses and comparison between the groups shall be performed through the t-test. Frequency between groups will be calculated and analyzed through the chi-square test or the Fisher's exact test in order to compare groups for categorical data.

Difference between groups regarding baseline observation values including demographic data of subjects will be observed in order to determine the pure treatment effect between test group and control group. Difference in demographic data or baseline observation values between test group and control group will result in such difference being considered as a disturbance factor should it be determined as being relevant to the effectiveness evaluation variables which is to be processed through subgroup analysis or being included in the effectiveness analysis as a covariate.

### **7.2.4 Effectiveness Analysis**

The knee joint with greater value in terms of 100mm Pan VAS shall be selected as the subject knee joint if both knee joints of the subject meets the selection criteria. If the 100mm Pain VAS values are the same for both knee joints, the knee joint with a more severe arthritis as determined by the investigator shall be selected as the subject knee joint.

#### **7.2.4.1 Primary Effectiveness Analysis**

- Change in 100mm Pain VAS on 28th day compared to baseline

Calculate the upper limit(97.5% one-sided confidence interval) for 95% two-sided confidence interval for the difference in change of 100mm Pain VAS on the 28th day compared to baseline of test and control groups(Average change in test group - Average change in control group). If the upper limit of the confidence interval is below 15mm, then it shall be determined that the test group is not inferior compared to the control group. For this, configure the change in 100mm Pain VAS as dependent variable with the administration group as the random factor, and the baseline 100mm Pain VAS as the covariate to perform the covariance analysis. Suggest the calibrated average for the change in 100mm Pain VAS for each administration group based on this analysis and suggest the difference in calibrated means between the two group and its 95% confidence interval.

Additionally, mean, standard deviation, minimum and maximum values shall be suggested for the amount of 100mm Pain VAS measured at each visit for the test group and the control group and the change in 100mm Pain VAS on the 28th day compared to baseline.

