### 3.2.2 Basis of Calculation

The primary purpose of this clinical trial is to prove noninferiority of test group compared to control group within clinical tolerance limit regarding the effect of pain relief evaluated by 100mm Pain VAS compared to baseline after administering the study drug or control drug for 28 days.

This clinical trial inferred from the study results of aceclofenac tablet(Aceclofenac vs paracetamol in the management of symptomatic osteoarthritis of the knee : a double-blind 6-week randomized controlled trial. Osteoarthritis and Cartilage 2007;15(8):900-908) in order to calculate the number of subjects necessary to prove noninferiority for this clinical trial. As a result of clinical trial conducted on patients with osteoarthritis of the knee for

aceclofenac tablet in terms of change in 100mm Pain VAS and standard deviation was  $-18.34 \pm 24.86$ mm and the combined standard deviation for this clinical trial based on this result was established as  $\pm 24.86$ mm and clinical tolerance was established as -15mm which came from references.

The following assumptions and hypotheses were established in order to prove noninferiority within clinical tolerance limit in terms of change in test group compared to that of control group.

- (1) Level of significance,  $\alpha=0.025$  (One-sided test)
- (2) Power of the test,  $1-\beta=0.975$
- (3) Test group to control group ratio,  $\lambda=1$
- (4) Standard deviation between test and control groups,  $\sigma_t=\sigma_c=24.86$ m
- (5) Clinical tolerance for noninferiority test,  $\delta=-15$ mm
- (6) Trace loss rate is assumed to be 10% ( $r=0.10$ )

Hypotheses of the noninferiority test for verification are as below.

$$H_0 : \mu_t - \mu_c \geq \delta$$

$$H_1 : \mu_t - \mu_c < \delta$$

The test variables required for the clinical trial are as below assuming (1)~(5) are true.

$$n_t = \frac{(\sigma_t^2 + \sigma_c^2)(Z_{1-\alpha} + Z_{1-\beta})^2}{\delta^2}$$

Number of subjects required per group according to equation above is 85 and it becomes 95 people per group considering the dropout rate of 10%.

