## **4.2 Procedure by Visit**

### **4.2.1 Visit 1(Screening and Washout Period, 14 Days Prior to Trial)**

Subjects selected for participation in this study shall be evaluated according to following sequence after listening to description of the study.

- 1) Describe trial procedure to subject and receive written consent form from subject prior to participation.
- 2) Assign screening number to subject in sequence of consent.
- 3) Survey and record demographic data and medical/medication history(Past and current history including surgeries).
- 4) Measure vital signs and weight and conduct physical examination.
- 5) Measure weight.
- 6) Conduct laboratory tests(Hematologic test, blood chemistry test, urine test, blood coagulation test).
- 7) Conduct pregnancy test for female subjects of childbearing age.
- 8) Perform ECG.
- 9) Conduct x-ray examination.
- 10) Evaluate according to ACR diagnosis criteria.
- 11) Evaluate according to inclusion/exclusion criteria.
- 12) Stop administration if subject is being regularly medicated with pain reliever and such and train on the washout period over 3~14 DAYS.

- 13) Evaluate 100mm Pain VAS.
- 14) Prescribe rescue drug.
- 15) Train on rescue drug log writing and distribute rescue drug log.
- 16) Schedule next visit.

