## **5. SUBJECT SELECTION AND DROPOUT CRITERIA**

### **5.1 Inclusion Criteria**

Patients meeting the following conditions are selected as subjects.

1. Male and female patients between age 35~80
2. Patients diagnosed with osteoarthritis of the knee according to ACR diagnosis criteria with Kellgran & Lawrence stage I~III diagnosis on x-ray imaging
3. Patients evaluated with osteoarthritis to be stable for 3 months prior to clinical trial by clinical physician
4. Patient with at least 40mm on 100mm Pain VAS scale during visit 2
5. Patients who voluntarily gave consent in written form to participate in this clinical trial

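### The Visit 1 pain VAS is collected before randomisation but is not in the primary ANCOVA; adding it as a second prespecified covariate may narrow the deciding confidence interval at almost no cost

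*Protocol*

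**What the plan says.** The Clinical Trial Schedule lists the 100 mm pain VAS at Visits 1, 2, 3 and 4. The procedures agree: section 4.2.1 includes "Evaluate 100mm Pain VAS" among the Visit 1 steps, and section 4.2.2 repeats the assessment at Visit 2 before the randomisation step. Entry depends on the second reading (section 5.1, item 4): "Patient with at least 40mm on 100mm Pain VAS scale during visit 2".

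Section 7.2.4.1 models the Day 28 change with treatment group as the factor and "the baseline 100mm Pain VAS as the covariate to perform the covariance analysis". No other covariate is named and baseline is not tied to a visit. The Visit 1 VAS appears only in the by-visit descriptive summary. The decision rule is "If the upper limit of the confidence interval is below 15mm", taken from the 95% interval for test minus control. Section 7.2.4.2 applies the same method to Day 14.

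Section 7.2.3 lets other baseline variables enter as covariates, but only once a difference between the groups has been seen and judged relevant to the effectiveness variables.

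**The concern.** The width of the interval for the adjusted difference depends on the residual SD after covariate adjustment. A second pre-treatment reading of the same outcome can explain part of the variation that a single noisy reading leaves. Here that reading is scheduled for every subject and precedes randomisation, yet the primary model does not use it.

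What is at stake is precision on the limit compared with 15 mm, and on the Day 14 comparison that inherits the model. Validity is not in question. Prespecifying the covariate would also be sounder than the route in section 7.2.3, where additions follow from observed imbalance.

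**Working it through.** **Inputs from the protocol (section 3.2.2).** One-sided alpha 0.025; power 0.975; SD of change 24.86 mm in both arms; margin 15 mm in size ("clinical tolerance was established as -15mm which came from references"); 1:1 allocation; 10% dropout. The formula has only the squared margin in its denominator, so the true difference is taken as 0.

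**The plan's own figure.** n per group = 2 × 24.86² × (1.96 + 1.96)² / 15² = 84.4, rounded up to 85. This matches "Number of subjects required per group according to equation above is 85". With 10% dropout, 85 / 0.9 = 94.4, giving 95, which also matches.

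**Starting precision.** SE = 24.86 × √(2/85) = 3.81 mm. Half-width = 1.96 × 3.81 = 7.47 mm. Power at a true difference of 0 is Φ(15/3.81 − 1.96) = 97.6%. This takes 24.86 mm, an SD of raw change, as the residual SD. If the residual SD after baseline adjustment is smaller, every millimetre figure below shrinks in proportion.

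**Effect of adding Visit 1.** The SE is multiplied by √(1 − p²), where p is the partial correlation of Visit 1 and Day 28 VAS given Visit 2:

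p = (r₁₄ − r₁₂ r₂₄) / √[(1 − r₁₂²)(1 − r₂₄²)]

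Subscripts 1, 2 and 4 denote the visits. The correlations are assumptions, since the protocol gives none. If all three equal r, then p = r/(1 + r).

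| r₁₂ / r₁₄ / r₂₄ | p | SE factor | Half-width (mm) | Power at difference 0 |
|---|---|---|---|---|
| 0.3 / 0.3 / 0.3 | 0.231 | 0.973 | 7.27 | 98.1% |
| 0.5 / 0.5 / 0.5 | 0.333 | 0.943 | 7.05 | 98.7% |
| 0.7 / 0.7 / 0.7 | 0.412 | 0.911 | 6.81 | 99.1% |
| 0.7 / 0.4 / 0.5 | 0.081 | 0.997 | 7.45 | 97.7% |
| 0.6 / 0.3 / 0.5 | 0 | 1.000 | 7.47 | 97.6% |

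In the last row the numerator is 0.3 − 0.6 × 0.5 = 0, so Visit 1 adds nothing. In sample-size terms, 85 × (1/f² − 1) gives about 5, 11 and 17 extra evaluable subjects per arm for the first three rows.

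**Subjects who skip washout.** Section 3.1 lets them go on to dosing, and no minimum gap between Visits 1 and 2 is stated for them. In a simulation in which half the subjects had identical Visit 1 and Visit 2 scores, the factor at r = 0.5 weakened from 0.943 to 0.976 (half-width about 7.29 mm).

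**The 40 mm entry cut.** The simulation used 2,000,000 normal draws per scenario, with an assumed VAS SD of 22 mm and Visit 2 mean of 58 mm. At r = 0.5 the cut reduced the SD of Visit 2 VAS from 22.0 to 16.7 mm. The residual SD given Visit 2 was 19.06 mm with and without the cut, and the SE ratio from adding Visit 1 was 0.943 both ways.

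**If the true difference is not 0.** At 85 per arm and SD 24.86 mm, for assumed true differences against the test drug:

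- 3 mm: power is Φ(12/3.81 − 1.96) = 88.2%, rising to 91.6% at factor 0.943.
- 5 mm: power is Φ(10/3.81 − 1.96) = 74.6%, rising to 79.4% at factor 0.943.

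With a residual SD of 20 mm the same comparisons are 97.5% to 98.6%, and 90.3% to 93.3%.

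**The case against.** The strongest case against acting is that nothing is wrong here. ANCOVA on a baseline of the same measure is a valid, prespecified model, and extra prognostic covariates are often left to the SAP. The design already has 97.5% power at a true difference of 0, calculated from an unadjusted SD. The gain is at most about 0.66 mm against a 15 mm margin, and it rests on correlations that the protocol does not give. Visit 1 may also predict poorly: for treated subjects it comes before washout, and for others it may nearly repeat Visit 2.

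Most of this stands. It limits the point to an optional improvement whose size starts at zero. It does not remove the point, because section 7.2.4.1 itself fixes the covariate, the extra data are already scheduled, and the change carries no bias.

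Three stronger readings may tempt a reader, and the protocol supports none of them:

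- **The 40 mm cut makes Visit 2 a weaker covariate, so precision is lost.** The cut does narrow the range of Visit 2 scores and lowers their correlation with the outcome. Under a linear model it changes neither the residual SD given Visit 2 nor the gain from Visit 1, and the residual SD sets the interval width.
- **A gain is certain.** Plausible correlations such as 0.6 / 0.3 / 0.5 give none.
- **Visit 1 shows pain in the same treated state as Day 28.** Washout under section 3.1 also covers narcotic analgesics, supplements, physical therapy and oriental therapy, and some subjects arrive untreated. Visit 1 is therefore not uniformly a score taken on an NSAID.

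**Conclusion.** The point holds as an optional efficiency gain. A second pre-randomisation VAS is available and unused, and including it cannot bias the comparison. With equal between-visit correlations of 0.3 to 0.7, the SE falls by about 3% to 9% and the upper limit tightens by about 0.2 to 0.7 mm, on the assumption that 24.86 mm is the residual SD. At a true difference of 0 this adds 0.5 to 1.5 points of power. It matters more if the test drug is truly a few millimetres worse. If Visit 1 carries little beyond Visit 2, the gain is close to nil.

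Separately from the size of the gain, baseline should be tied to a visit, because two pre-treatment VAS readings exist. Visit 2 is the natural reading but is not stated.

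**What to change.** In section 7.2.4.1, define baseline as the Visit 2 VAS and write the primary model as: change = treatment + Visit 2 VAS + Visit 1 VAS + washout done (yes/no). Optionally add a Visit 1 VAS by washout interaction, since an additive model forces one Visit 1 slope on washed-out and untreated subjects alike. Fix the model before unblinding and use it for Day 14 in section 7.2.4.2 as well.

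The cost is a line or two of wording and one to three degrees of freedom out of 167 (170 evaluable subjects less intercept, treatment and baseline). No new data are needed, and the sample size and the 15 mm rule do not change.

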#### **7.2.4.2 Secondary Effectiveness Analysis**

- 1) Change in 100mm Pain VAS on 14th day compared to baseline

Analysis through application of the same statistical method as the primary effectiveness evaluation variables.

- 2) Change in K-WOMAC scale on 14th and 28th day compared to baseline

Verify through the paired t-test for changes in total K-WOMAC score along with pain subscale, stiffness subscale, and physical function subscale on the 14th and the 28th days between test group and control group compared to the baseline.

Also, use the t-test to verify whether there is a difference between groups in terms of change on the 14th and the 28th day compared to baseline for each item.

- 3) Patient Global Assessment

Suggest the frequency and percentage of subjects evaluated as 'Very good(5)', 'Good(4)', 'No change(3)', 'Poor(2)', and 'Very poor(1)' on the 14th and the 28th day after investigational product administration and perform the chi-square test or the Fisher's exact test to see if there is a difference between groups.

If the overall assessment scores are 5 or 4, categorize as 'Response' and 'No response' if the scores are 3, 2, or 1 to suggest treatment response rates for each group. Perform the chi-square test or the Fisher's exact test to check for difference in treatment response rate between groups.

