##### **4.1.1.3 Patient Global Assessment**

Subjective severity of disease and overall improvement in osteoarthritis of the knee will be evaluated using the following 5 point rating scale by the subject for final evaluation of effectiveness.

- 5 : Very good
- 4 : Good
- 3 : No change
- 2 : Poor
- 1 : Very poor

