#### **7.1.2 Secondary Effectiveness Evaluation Variables**

- 1) Change in 100mm Pain VAS on 14th day compared to baseline
- 2) Change in K-WOMAC scale on 14th and 28th day compared to baseline
- 3) Patient Global Assessment
- 4) Frequency of rescue drug usage

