#### **7.2.2 General Statistical Principles**

Verification of all statistical significance shall be performed by a two-tail test

with significance level( $\alpha$ ) of 5%. However, noninferiority will be verified using the confidence interval.

Main analysis of data regarding effectiveness from subjects of this clinical trial shall be performed through PPS followed by additional analysis of FAS by principle.

Analysis of data regarding safety shall be performed through the safety analysis set.

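### The five ordered grades of the Patient Global Assessment are compared with a test that ignores their order; an ordinal test would usually be more sensitive to a consistent shift, at no extra data cost

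*Protocol*

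**What the plan says.** Protocol section 4.1.1.3 defines the outcome: "Subjective severity of disease and overall improvement in osteoarthritis of the knee will be evaluated using the following 5 point rating scale", with grades running from 5 (very good) through 3 (no change) to 1 (very poor). Section 7.1.2 lists it as the third of four secondary effectiveness variables.

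Section 7.2.4.2, item 3, plans two between-group comparisons:

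- The frequency and percentage in each of the five grades are shown at Days 14 and 28, and the instruction is to "perform the chi-square test or the Fisher's exact test to see if there is a difference between groups".
- The scale is then cut in two: "If the overall assessment scores are 5 or 4, categorize as 'Response' and 'No response' if the scores are 3, 2, or 1". Response rates are compared, again by chi-square or Fisher's exact test.

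Section 7.2.2 sets the framework for these tests: "Verification of all statistical significance shall be performed by a two-tail test", at the 5% level. No power target, expected distribution or effect size is given for this outcome. The sample size in section 3.2.2 rests on the pain VAS alone.

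**The concern.** A chi-square test on a 2 by 5 table has 4 degrees of freedom and responds to any departure between the two sets of proportions. It treats a move from good to very good and a move from good to very poor as the same kind of event. The main question for a global improvement rating is whether one group tends to fare better or worse, and for that question the test spreads its sensitivity over many other patterns.

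What is at stake is the chance of detecting a real shift in patients' own rating, in either direction. The protocol names the test itself, so this is a stated choice and not a detail left to an analysis plan that is not at hand. A better-suited test uses the same data.

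**Working it through.** **Inputs from the protocol.** Five ordered grades (4.1.1.3). Two-sided 5% (7.2.2). 85 evaluable and 95 randomised per group, 1:1 (3.2.1, 3.2.2).

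**The plan's own figure.** n = (σt² + σc²)(z₀.₉₇₅ + z₀.₉₇₅)² / δ² = 2 × 24.86² × (1.96 + 1.96)² / 15² = 84.4, rounded up to 85. Then 85 / 0.90 = 94.4, rounded up to 95. The planned size reproduces. It concerns the VAS only.

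**Assumptions, because the documents give neither.**

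- *Control-arm distributions*, grades 1 to 5 in percent: A 5/10/30/40/15; B 2/8/30/45/15; C 20/20/20/20/20; D 1/4/25/55/15; E 3/7/20/50/20.
- *Difference between arms*: a common odds ratio (OR). Each cumulative odds c/(1 − c) of the control arm is divided by the OR. Example, A at OR 2: control cumulative proportions 0.05, 0.15, 0.45, 0.85 become 0.026, 0.081, 0.290, 0.739. The share in grades 4 and 5 rises from 55% to 71%.

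**Method.** Simulation of 20,000 trials per setting with 85 per arm, comparing the Pearson 2 by 5 chi-square, the tie-corrected Wilcoxon rank-sum test, and the 2 by 2 chi-square on response (4–5 against 1–3). At OR 1 the three tests rejected in 3.6% to 5.3% of trials, so none exceeds its level materially. Fisher's exact test on the 2 by 5 table was not simulated.

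**Power, percent.** The first three result columns are for distribution A. The last is the Wilcoxon minus chi-square gap over all five distributions, in percentage points.

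| OR | 5-grade chi-square | Wilcoxon | Responder test | Gap, A to E |
|---|---|---|---|---|
| 1.25 | 8.0 | 12.4 | 11.2 | 4.4–5.6 |
| 1.5 | 17.0 | 30.3 | 25.6 | 12.4–13.3 |
| 1.75 | 30.7 | 50.5 | 41.9 | 18.6–20.4 |
| 2.0 | 45.7 | 68.7 | 57.5 | 22.3–23.4 |
| 2.25 | 60.4 | 81.3 | 70.7 | 19.8–21.9 |
| 2.5 | 72.4 | 89.8 | 80.1 | 15.5–18.4 |
| 3.0 | 88.3 | 97.1 | 91.1 | 7.4–10.2 |
| 4.0 | 98.3 | 99.8 | 98.0 | 1.2–2.1 |

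**Against the planned responder test.** At OR 2 the Wilcoxon gains 8.8 to 18.7 points over A to E. A control arm of 5/15/40/30/10 percent, with 40% responders, gives the smallest gain seen (Wilcoxon 69%, responder test 62%). Allowing for simulation error, the range is about 6 to 19 points.

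**With 95 per arm.** Distribution A at OR 2: chi-square 50.8%, Wilcoxon 73.2%, responder test 62.7%. The picture does not depend on which of the two planned group sizes is used.

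**When the difference is not a consistent shift.** Control 5/10/30/40/15 against 12/8/15/40/25 percent, so both extremes gain patients: chi-square 67%, Wilcoxon 20%. The ranking reverses.

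**The case against.** The planned test is valid. It holds its level, and it answers the question that section 7.2.4.2 literally asks, whether the groups differ. The outcome is one of four secondary variables, with no power target. The sample-size formula assumes no true difference between the drugs, so odds ratios near 2 lie outside the planning scenario. The same section already plans a responder comparison that uses the order in part. All of this stands, and it keeps the point small.

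Four stronger readings are tempting, and the documents do not support them.

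- *A flat loss of about 20 points.* That size holds only for odds ratios of roughly 1.75 to 2.25, near the maximum gap, and the documents supply no effect size. It also leaves out the responder test, which recovers part of the loss.
- *A gain for free.* It costs no patients or data, but it requires a consistent shift. For a polarised difference the chi-square is the better test, and such a pattern is not clinically meaningless.
- *A weak secondary test favours the sponsor's conclusion.* Nothing in the protocol says that a non-significant result on this outcome counts as evidence of similarity. A non-significant rank test could be misread in the same way.
- *The noninferiority claim is weakened.* Section 7.2.4.1 decides it by the confidence interval for the VAS change, which does not involve this outcome.

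**Conclusion.** The point holds as an optional improvement. Section 4.1.1.3 defines an ordered scale, and section 7.2.4.2 names an unordered test for it. At 85 per arm and two-sided 5%, a rank test has about 12 to 23 points more power than the five-category chi-square under an assumed common odds ratio of 1.5 to 2.5. The advantage is about 4 to 6 points at odds ratio 1.25 and 7 to 10 at odds ratio 3. Against the planned responder test it is about 6 to 19 points at odds ratio 2.

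These figures rest on assumed grade distributions and on a shift in one direction across the whole scale. Without such a shift the advantage can disappear or reverse. The primary conclusion does not change.

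**What to change.** In section 7.2.4.2, item 3, name the Wilcoxon rank-sum test as the between-group test of the five grades at Days 14 and 28. A Cochran-Mantel-Haenszel row-mean-score test with rank-based scores would serve equally; with the raw 1 to 5 scores it is not the same test. Keep the frequency table, and keep the responder-rate comparison as a planned test.

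The cost is one line of analysis text, with no new data, visits or patients. The price is lower sensitivity to a polarised difference, where very good and very poor ratings both become more common. The retained frequency table would still show it.

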| Confirmation of pain reliever administration stoppage        |                             | X                     |         |         |
| Random assignment                                            |                             | X                     |         |         |
| 100mm Pain VAS assessment                                    | X                           | X                     | X       | X       |
| K-WOMAC assessment                                           |                             | X                     | X       | X       |
| Patient Global Assessment                                    |                             |                       | X       | X       |
| Adverse events                                               |                             |                       | X       | X       |
| Confirmation of change in co-administered drugs  |                             |                       | X       | X       |
| Prescription of investigational product                      |                             | X                     | X       |         |
| Rescue drug prescription and distribution of rescue drug log | X                           | X                     | X       |         |
| Survey on frequency of rescue drug usage                     |                             | X                     | X       | X       |

- 
- 1 For subjects administered and treated with non-steroid anti-inflammatory pain reliever, osteoarthritis supplements, physical therapy, and oriental therapy(Acupuncture, cupping, moxibustion) within 2 weeks prior to screening must stop such administration and treatment for 14 days for a washout period and subjects without administration and treatment within the past 2 weeks can be administered with investigational products without having a washout period.
  - 3 It can be substituted with test results within 3 months from screening date.
  - 4 It can be substituted with test results within 4 weeks from screening date.

|                      |                                                                                                                                                                                     |
|----------------------|-------------------------------------------------------------------------------------------------------------------------------------------------------------------------------------|

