### **7.2 Plan for Statistical Analysis**

#### **7.2.1 Definition of Analysis Sets**

Analysis sets are defined as below.

- (1) Safety analysis set: It consists of randomly assigned subjects who have been medicated with investigational products at least once.
- (2) FAS (Full Analysis Set): It consists of subjects that yield data on primary effectiveness evaluation variables who have been medicated with investigational products at least once.
- (3) PPS (Per-Protocol Set): It consists of subjects who completed the trial according to the clinical trial plan among subjects included in the FAS.

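### The main Patient Global Assessment response rate is taken among completers, so treatment failures who stop early leave it, and the FAS with LOCF repairs this only in part.

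*Protocol*

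**What the plan says.** Protocol 7.2.4.2, item 3, turns the five-point Patient Global Assessment into a response rate and compares it between groups by a chi-square or Fisher's exact test. The rule is: "If the overall assessment scores are 5 or 4, categorize as 'Response' and 'No response' if the scores are 3, 2, or 1". It covers scores 1 to 5 and is silent on a subject with no score.

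The population comes from 7.2.2: "Main analysis of data regarding effectiveness from subjects of this clinical trial shall be performed through PPS followed by additional analysis of FAS". Section 7.2.1 defines the PPS: "It consists of subjects who completed the trial according to the clinical trial plan among subjects included in the FAS". The FAS in the same section needs at least one dose and data on the primary variable.

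The remaining provisions that bear on leavers are:
- 7.2.6 carries the last observation forward after dropout or for a missing value, in the FAS analysis only.
- The Clinical Trial Schedule places the Patient Global Assessment at Visits 3 and 4 only, with no baseline rating.
- 4.2.4 has the Visit 4 items, including this assessment, done also when a subject ends early.
- 5.3 has the investigator ask leavers for a last visit, so attendance is sought but not assured.

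No provision counts a leaver as 'No response'.

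**The concern.** A response rate should give the share of treated subjects who responded. Someone who stopped by Day 28 because the drug did not work or was not tolerated has not responded to it, yet the main analysis drops that person from both the count of responders and the total.

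The protocol expects such leavers. Section 9.5 provides other care for subjects who do not respond. Section 6.7.2 restricts pain relievers other than the rescue drug and requires a subject who needs a restricted drug to stop, and 5.4 removes users of prohibited drugs from the PPS. Section 7.2.5.1 reports adverse reactions that cause stoppage. The subjects removed are therefore unlikely to be a random subset.

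At stake is the size of the reported response rate and, if leaving differs between arms, the comparison. An arm that loses more failures is flattered.

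**Working it through.** **The plan's own figure.** Section 3.2.2 gives an SD of 24.86 mm per group, a margin of 15 mm in absolute size, one-sided alpha 0.025 and power 0.975. Then n = 2 × 24.86² × (1.96 + 1.96)² / 15² = 84.41, rounded up to 85. Allowing for loss, 85 / 0.90 = 94.4, rounded up to 95 per group. Both stated figures reproduce. None of this depends on the Patient Global Assessment.

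**Inputs for this point.** From the protocol: 95 per group, and "Trace loss rate is assumed to be 10" per cent for the trial as a whole. The protocol gives no response rate for this variable and no loss by arm. Assumptions: response rates of 40% to 70%, various splits of the leavers, and every leaver truly a non-responder. The true rate means responders divided by all treated subjects.

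**PPS, by proportion.** Completer rate = true rate / (1 − share leaving).
- 10% leaving, true 50%: 0.50 / 0.90 = 55.6%.
- 15% v 5% leaving (average 10%), true 50% in both arms: 0.50 / 0.85 = 58.8% v 0.50 / 0.95 = 52.6%, a spurious 6.2 points.
- The same split, true 45% v 50%: 0.45 / 0.85 = 52.9% v 52.6%, so a 5-point deficit disappears.

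**PPS, by counts.** Take 57 responders of 95 in each arm (60.0%) and 19 or 20 leavers in total.
- 10 v 10 leavers: 57/85 = 67.1% in both arms, difference 0.
- 14 v 5: 57/81 = 70.4% v 57/90 = 63.3%, difference 7.0 points (from unrounded rates).
- 19 v 0: 57/76 = 75.0% v 57/95 = 60.0%, difference 15.0 points, as an extreme.

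For 14 v 5, as the true rate goes from about 40% to about 70% (38 to 67 responders of 95), the spurious difference goes from 4.7 to 8.3 points.

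**FAS with LOCF.** Same 57 responders per arm and 14 v 5 leavers.
- All leavers scored, all 1 to 3: 57/95 in both arms, difference 0.
- Half scored, all 1 to 3: 57/88 = 64.8% v 57/92.5 = 61.6%, difference 3.2.
- All scored, a quarter of them 4 or 5: 60.5/95 = 63.7% v 58.25/95 = 61.3%, difference 2.4.
- All scored, half of them 4 or 5: 64/95 = 67.4% v 59.5/95 = 62.6%, difference 4.7 (from unrounded rates).
- None scored: as in the PPS, difference 7.0.

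**With leavers counted as 'No response'** in all treated subjects, both arms are 57/95 and the difference is 0 in each of these scenarios.

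**The case against.** A reader might infer that a subject who leaves because the drug failed is never a non-responder under this plan, and that the arm with more leavers must look better. The documents do not support that. Section 4.2.4 collects the assessment at premature end, 5.3 seeks a last visit, and 7.2.6 carries the score forward in the FAS. A leaver who attends and scores 1 to 3 is counted as 'No response' there. Bias between arms needs unequal leaving, and the protocol gives one loss rate, not a split. Nor is overstatement in both arms certain: it depends on leavers being failures and, in the FAS, on their being unscored or scored 4 or 5.

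Other objections also have weight:
- PPS exclusions include eligibility violations and missed examinations (5.4), which are not treatment failures.
- The assumed 6-point shift is below one standard error at 85 per arm: √(2 × 0.55 × 0.45 / 85) = 7.6 points.
- Harm is not hidden, since stoppages for adverse reactions are reported by group in the safety set.
- Counting every leaver as a non-responder is one strategy among several.
- Handling of missing secondary data is often left to the SAP, which is not shown.

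These limit the point but do not remove it. The protocol itself fixes the completer set as the main one and LOCF as the FAS rule, so this is more than a detail left open. The FAS is the additional analysis and keeps two gaps: a last score of 4 or 5 before a stop for harm, and leaving before Visit 3 with no exit rating. In the second case the subject may not even meet the FAS definition.

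**Conclusion.** The point holds in a limited form. Followed as written, the main response rate describes completers, not treated subjects. Under the assumption that all leavers are failures, the plan's 10% loss lifts a true 50% to 55.6%. An assumed 15% v 5% split creates a 6-point difference between equal arms in the PPS. With equal leaving and equal true rates there is no difference between arms. In the FAS the distortion ranges from none to the full PPS size, and is smaller when leavers have exit scores. The response rates, the split and the status of leavers are all assumptions.

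The variable is the third of four secondary ones. The primary non-inferiority conclusion and the sample size do not depend on it, so this is a cheap improvement to a secondary analysis.

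**What to change.** In 7.2.4.2, item 3, state that the Day 28 response comparison is made in all randomised and dosed subjects by assigned group, and that a subject who stopped assigned treatment early or has no Day 28 rating counts as 'No response'. Keep the PPS and FAS/LOCF rates as supportive analyses, so that the exit ratings collected under 4.2.4 are still used.

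The cost is a sentence or two in the protocol and no new data. The downside is somewhat lower reported response rates, with some subjects lost for unrelated reasons counted as non-responders. The supportive rates show how much that matters.
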